## Abstract

Background: Chronic pelvic toxicity induced by radiotherapy and/or chemotherapy (R/CIPT) is a debilitating sequela in gynecological cancer survivors, often refractory to conventional treatments and potentially linked to gut microbiota dysbiosis. Ozone therapy (OT), particularly rectal insufflation, demonstrates anti-inflammatory and redox-modulating effects through hormetic mechanisms (Nrf2 activation/NF-κB inhibition). We hypothesize that its clinical benefit is mediated, in part, by restoring gut microbial homeostasis. Objective: This manuscript proposes a clinical study to evaluate the impact of rectal OT on the gut microbiota of patients with gynecological cancers and chronic R/CIPT. Proposed Methods: A prospective, observational study of 38 patients is outlined: 19 with CTCAE v5.0 Grade ≥2 chronic R/CIPT receiving compassionate rectal OT (~40 sessions over 4 months), and 19 matched controls without toxicity. Stool samples for 16S rRNA sequencing will be collected from the OT group pre- and post-intervention and once from controls. Primary endpoints are changes in microbiota composition/diversity and pelvic toxicity scores (CTCAE v5.0, EORTC QLQ-CX24). Secondary endpoints include quality of life (EORTC QLQ-C30, EQ-5D-5L), anxiety/depression (HADS), and serum inflammatory/oxidative stress biomarker analysis. Anticipated Results and Conclusion: This will be the first study to prospectively investigate whether rectal OT’s effect correlates with a beneficial shift in the gut microbiota, specifically an increase in commensals (e.g., short-chain fatty acids producers) and a decrease in pathobionts. If successful, OT could be assessed as a novel, microbiota-targeting intervention for R/CIPT. The findings from this pilot study will provide the necessary groundwork for a future randomized controlled trial to definitively establish causality and efficacy.

## 1. Introduction

Gynecological cancers, especially malignancies of the endometrium, uterine cervix, vagina, and vulva, represent a significant health burden worldwide, with radiotherapy (RT) and chemotherapy (QT) forming the cornerstone of treatment strategies [1,2]. Despite their effectiveness in improving survival, these therapies are frequently associated with acute and chronic toxicities, particularly when the pelvic region is irradiated. Among these, genitourinary (such as chronic mucosal ulcers, gynecological pain, cystitis, and vesical bleeding) and gastrointestinal (GI) side effects (such as diarrhea, pelvic pain, enteritis, proctitis, and rectal bleeding) markedly impair patients’ quality of life. Many times, these symptoms are refractory to conventional treatments [3,4].

Emerging evidence suggests that the intestinal microbiota plays a central role in mediating host responses to oncological treatments [5,6]. Pelvic RT and cytotoxic QT induce profound dysbiosis, characterized by reduced microbial diversity and shifts in protective taxa. These alterations are increasingly recognized as contributors not only to local GI toxicity but also to systemic inflammation and variable therapeutic efficacy. Consequently, interventions capable of preserving or restoring a balanced gut microbiota during oncological treatment are of growing clinical interest [7,8].

Ozone therapy (OT), a medical approach based on controlled administration of an oxygen–ozone mixture, has gained attention as a supportive treatment in oncology [9]. Its pleiotropic effects include modulation of redox signaling, enhancement of tissue oxygenation, anti-inflammatory activity, and regulation of immune responses. Clinical studies have reported that OT can reduce fatigue, improve quality of life, and mitigate adverse effects associated with RT and QT [10,11]. More recently, preclinical studies suggest that ozone administration, particularly through rectal insufflation, may directly or indirectly influence the gut microbial ecosystem [12,13]. This observation is consistent with the therapy’s known capacity to modify mucosal oxidative balance, microcirculation, and local immune milieu.

To date, however, the relationship between OT, gut microbiota composition, and the mitigation of RT/QT-induced toxicity in gynecological patients remains largely unexplored. Understanding this interplay is crucial, as it may open new avenues for reducing treatment-related morbidity and optimizing patient outcomes. This manuscript aims to (i) review current knowledge on the impact of RT and QT on gut microbiota in gynecological cancers, (ii) explore mechanistic insights into how OT may modulate microbial and host responses, and (iii) propose a clinical framework to investigate OT as an adjuvant strategy for managing therapy-induced toxicity. By addressing these objectives, we intend to provide a scientific rationale for integrating microbiome analysis into supportive oncology protocols and highlight the potential of OT as a novel adjunctive tool.

## 2. Radiotherapy and Chemotherapy Effects on Gut Microbiota

### Evidence of Dysbiosis in Patients Undergoing Pelvic RT/QT

The human gut microbiota, a complex ecosystem of trillions of microorganisms, plays a fundamental role in maintaining host health. It is involved in nutrient metabolism, protection against pathogens, and the regulation of immune function. In oncology, RT and QT are cornerstone treatments, but they are notoriously damaging to healthy, rapidly dividing cells—including those lining the GI tract. The detrimental effects of these treatments on the gut microbiota, a state known as “dysbiosis”, are now recognized as a major contributor to side effects and a potential modulator of treatment efficacy [3,4]. This discussion will focus on the evidence linking pelvic RT and systemic QT to significant alterations in the gut microbiota, the mechanisms behind this dysbiosis, and its clinical consequences.
(a)*Defining the Insult: How RT and QT Disrupt the Gut Ecosystem.*

The mechanisms by which these therapies damage microbiota are multifaceted:
–Direct Cytotoxicity: Both RT and QT are designed to kill rapidly dividing cells. While their target is cancer, they also attack the rapidly renewing epithelial cells of the intestinal lining [14,15]. This damage compromises the integrity of the mucosal barrier, creating an inflamed environment that is hostile to beneficial, obligate anaerobic bacteria (e.g., *Faecalibacterium*, *Roseburia*) and favorable for pathobionts (potentially pathogenic bacteria) [16].–Indirect Effects via the Host: The destruction of the intestinal epithelium leads to a cascade of events: Mucus Layer Thinning: Goblet cells are damaged, reducing mucin production. This depletes the primary habitat and food source for many commensal bacteria. Inflammation: Cell death triggers a potent inflammatory response, releasing antimicrobial peptides and reactive oxygen species that further reshape the microbial community. Immune Dysregulation: The gut microbiota is in constant cross-talk with the immune system. Therapy-induced damage to immune cells in the gut-associated lymphoid tissue (GALT) disrupts this delicate balance [15,17].

(b)
*Evidence of Dysbiosis in Patients Undergoing Pelvic RT.*

Pelvic RT, used for cancers of the prostate, cervix, uterus, rectum, and anus, directly irradiates the lower GI tract, making it a prime model for studying microbiota disruption. The evidence for dysbiosis is robust and characterized by several consistent patterns:
–Loss of Microbial Diversity: A hallmark of a healthy gut is high species richness (alpha-diversity). Multiple studies have demonstrated a significant and rapid decrease in alpha-diversity in patients undergoing pelvic RT. This loss is considered a sign of ecosystem instability and is strongly correlated with the severity of GI symptoms, particularly diarrhea [18,19].–Shifts in Key Bacterial Taxa. Depletion of Beneficial Genera: There is a consistent and dramatic reduction in beneficial, short-chain fatty acid (SCFA)-producing bacteria. Butyrate producers like *Faecalibacterium prausnitzii* and *Roseburia* spp. are particularly vulnerable. Their loss is directly linked to mucosal barrier breakdown and inflammation [18,20].–Expansion of Pathobionts: Concurrently, there is an increase in opportunistic pathogens and pro-inflammatory bacteria. Commonly reported blooms include *Enterobacteriaceae* (e.g., *Escherichia*, *Klebsiella*) and an increased susceptibility to *Clostridium difficile* infection [21,22].–Dose–Response Relationship: The degree of dysbiosis is often correlated with the radiation dose delivered to the rectum and bowel. Higher doses are associated with more profound microbial shifts and worse clinical toxicity [20].–Persistence of Dysbiosis: Critically, these changes are not always transient. Studies following patients for months after RT have found that microbial diversity and the abundance of key beneficial species often fail to return to pre-treatment levels, suggesting long-term alteration of the gut ecosystem [18].

(c)
*Evidence of Dysbiosis in Patients Undergoing Systemic QT.*

While pelvic RT causes localized damage, systemic chemotherapy affects the entire GI tract. The evidence for QT-induced dysbiosis is equally compelling, though the specific changes can vary based on the chemotherapeutic agent.

Agent-Specific Effects:
–5-Fluorouracil (5-FU): Strongly associated with mucositis and a decrease in microbial diversity, particularly reducing SCFA producers [23].–Irinotecan: Causes severe diarrhea and is linked to a bloom of *Enterobacteriaceae* and a reduction in beneficial *Firmicutes* [24].–Cyclophosphamide: Interestingly, some chemotherapies like cyclophosphamide rely on a specific microbiota to stimulate anti-tumor immune responses. It can cause a translocation of specific Gram-positive bacteria to secondary lymphoid organs, priming pathogenic T-helper 17 (Th17) cells [25].

Common Themes in QT-Induced Dysbiosis:
–Reduced Diversity: Similar to RT, a drop in alpha-diversity is a common finding [23].–Impact on Treatment Outcomes: The microbiota can influence QT efficacy and metabolism. For instance, some gut bacteria can inactivate chemotherapeutic drugs, while others can convert prodrugs into their active forms [26].

(d)
*Clinical Consequences of Therapy-Induced Dysbiosis.*

The dysbiosis described above is not merely an observational finding; it has direct and serious clinical implications:
–RT/CT-Induced Diarrhea and Mucositis: The loss of SCFA producers and the expansion of pro-inflammatory bacteria directly contribute to these debilitating side effects [24].–Infection Risk: The loss of “colonization resistance” allows for the overgrowth of opportunistic pathogens like *C. difficile* [27].–Systemic Inflammation: A leaky gut and an abundance of LPS from Gram-negative bacteria can lead to bacteremia and systemic inflammation.

The evidence is clear: both pelvic radiotherapy and systemic chemotherapy induce profound and specific dysbiosis in the gut microbiota. This dysbiosis is a key driver of the acute and chronic toxicities that diminish patients’ quality of life. This growing understanding has opened exciting new avenues for supportive care in oncology, including:
–Microbiota as a Biomarker: Pre-treatment microbial signatures may predict a patient’s risk of developing severe toxicity [28].–Microbiome-Targeted Therapies: Interventions like probiotics, prebiotics, and fecal microbiota transplantation (FMT) are being actively investigated to prevent or reverse therapy-induced dysbiosis [28].

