## 5. Proposed Clinical Study/Protocol

Study Population. Primary Cohort (Group R/CIPT, Radiotherapy/Chemotherapy-Induced Pelvic Toxicity): Adult women (≥18 years) with gynecological malignancies (cervical, endometrial, vulvar, vaginal) who have received pelvic RT with/without CT and present with chronic pelvic toxicity (≥3 months duration) rated as Grade ≥2 according to the Common Terminology Criteria for Adverse Events (CTCAE) v5.0 from the U.S. National Cancer Institute. In our institution, these patients are usually referred for compassionate OT due to symptoms refractory to conventional treatment. Control Cohort: Gynecological cancer patients matched by age (±5 years) and primary tumor location, treated with R/CIPT but without symptoms of pelvic toxicity.

Intervention: Rectal Ozone Insufflation +/− direct local application to the affected mucosa (rectal, vesical, and/or vaginal), based on the standard treatment protocol of the Chronic Pain Unit for compassionate use of OT. Proposed Regimen: It usually consists of 40 sessions administered over 4 months, following the unit’s standard operating procedures. The ozone concentration (µgO_3_/mLO_2_) will start at 10 µg/mL and increase by 5 µg/mL every 2 sessions until it reaches 30 µg/mL by the 9th session, after which it will be maintained until week 16. The volume will start at 180 mL and will be progressively increased to 300 mL if tolerated. The total ozone dose will range from 1800 µg to 9000 µg. To address standardization, the rectal ozone insufflation procedure will use a sterile, flexible catheter (14–16 Fr, 20–25 cm), inserted 7.5–12 cm into the rectum after lubrication. The patient will be positioned on their side, and the oxygen-ozone mixture will be administered over 5 min. All procedures will follow the unit’s standard operating protocols and be performed by trained staff. This approach is supported by published clinical protocols and safety data [51].

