Inclusion Criteria for all study participants: (1) Adult women (≥18 years of age) with a histologically confirmed gynecological malignancy (cervical, endometrial, vulvar, or vaginal), of any stage, who have completed a course of pelvic RT and/or CT. (2) Ability to understand and willingness to sign the study-specific Informed Consent Form. Additional criteria for inclusion in the OT Group: Presence of chronic R/CIPT, with a duration of ≥3 months following conventional symptomatic management. A toxicity grade of 2 (moderate symptoms; limiting instrumental activities of daily living) or higher, as per the CTCAE v5.0.

Exclusion Criteria for all study participants: any of the following will preclude inclusion: (1) Failure to meet all the inclusion criteria specified above. (2) Unwillingness or inability to provide written informed consent for study participation. (3) Presence of active inflammatory bowel disease (e.g., Crohn’s Disease, Ulcerative Colitis) or a history of major gastrointestinal resection (excluding appendectomy) that could significantly alter gut anatomy and microbiota. (4) Any uncontrolled intercurrent illness or psychiatric condition that, in the investigator’s opinion, would limit compliance with study requirements or interfere with the interpretation of results.

Withdrawal Criteria. Participants will be withdrawn from the study under the following circumstances: (1) Voluntary Withdrawal: At the patient’s own request, at any time and for any reason, without any penalty or impact on their future clinical care. (2) Loss to Follow-up: Inability to contact the patient or their failure to attend scheduled study visits. (3) Clinical Decision: Withdrawal by the principal investigator due to the occurrence of an adverse event, intercurrent illness, or any other clinical reason that justifies discontinuation for the patient’s well-being or the integrity of the study. (4) Protocol Violation: Significant deviation from the study protocol.

All patients, regardless of their decision to participate, decline, or withdraw from the study, will continue to receive standard oncological care and follow-up from their treating physicians. Withdrawal from the study will not affect their access to routine or compassionate medical treatments, including ozone therapy if clinically indicated.

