The analysis of serum biomarkers will encompass a comprehensive panel to evaluate both oxidative stress and inflammatory status. 1. Oxidative Stress Biomarkers: The assessment will include global oxidative stress markers such as FRAP (Ferric Reducing Ability of Plasma), which measures antioxidant capacity; dROMs (Reactive Oxygen Metabolites), which determines the peroxidation potential; and BAP (Biological Antioxidant Potential). Specific molecular biomarkers will also be quantified, including the activity of the key antioxidant enzymes Superoxide Dismutase (SOD) and Catalase (CAT), the levels of reduced glutathione (GSH) as a critical cellular antioxidant, Advanced Oxidation Protein Products (AOPP) as a marker of protein damage, and ROOH (Total Hydroperoxides) to assess the primary oxidation products of lipids and other molecules. 2. Inflammatory Biomarkers: The inflammatory profile will be characterized by measuring a panel of Pro-inflammatory Cytokines: Tumor Necrosis Factor-alpha (TNF-α), Interleukin-6 (IL-6)**,** Interleukin-1 beta (IL-1β), and Interleukin-8 (IL-8/CXCL8)**.** Furthermore, systemic inflammation will be evaluated through established clinical markers: C-Reactive Protein (CRP) and VES (Erythrocyte Sedimentation Rate)**.**

Statistical Approaches: Primary Analysis: Non-parametric tests will be used due to the small sample size (Wilcoxon signed-rank for pre/post ozone, Mann–Whitney U for inter-group comparisons). Spearman correlations for microbiota-clinical parameter associations. All variables will be described as medians and quartiles 1–3 (percentiles 25–75%). *p*-values less than 0.05 will be considered significant, and all hypothesis tests will be conducted two-sided. Software: R (v4.5.0 or higher).

This study is the first to prospectively explore the novel hypothesis that the clinical benefits of rectal OT for chronic R/CIPT could be mediated, in part, through gut microbiota modulation. The proposed mechanistic pathway is: Ozone → Attenuation of local oxidative stress and inflammation (via Nrf2 activation and NF-κB inhibition) → Restoration of a healthy mucosal microenvironment → Promotion of commensal bacteria (e.g., SCFA producers) and suppression of pathobionts → Improved barrier function and reduced systemic inflammation → Clinical improvement in toxicity and Quality of Life.

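### The toxicity-versus-control microbiota contrast can be confounded by prior chemotherapy, which the control rule leaves free

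*Protocol article*

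**What the plan says.** **Background (Section 2).** Part (a) says that radiotherapy and chemotherapy both attack the renewing intestinal epithelium and weaken the mucosal barrier, to the disadvantage of genera such as Faecalibacterium and Roseburia. Part (c) states: "The evidence for QT-induced dysbiosis is equally compelling, though the specific changes can vary based on the chemotherapeutic agent". The examples that follow are fewer SCFA producers with 5-FU and an Enterobacteriaceae bloom with irinotecan. Part (d) concludes: "both pelvic radiotherapy and systemic chemotherapy induce profound and specific dysbiosis in the gut microbiota. This dysbiosis is a key driver" of acute and chronic toxicity.

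**Eligibility (Section 5).** The toxicity group consists of women "who have received pelvic RT with/without CT and present with chronic pelvic toxicity". The inclusion criteria for all participants admit women "who have completed a course of pelvic RT and/or CT".

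**Controls (Section 5).** They are "Gynecological cancer patients matched by age (±5 years) and primary tumor location", and "treated with R/CIPT but without symptoms of pelvic toxicity". Table 1 repeats the same two matching factors.

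**Analysis (Section 5, Statistical Approaches).** The plan gives "Mann–Whitney U for inter-group comparisons" and names no stratification or covariate. The limitations text lists antibiotics and probiotics as examples of confounders to be recorded; chemotherapy is not among them. The same text regards the single control sample as sufficient for a first comparison of women with and without chronic toxicity.

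**The concern.** On the article's own account, chemotherapy can shift the taxa that make up the primary microbiological endpoint, and it can injure the mucosa whose injury defines the toxicity group. Chemotherapy may be present or absent in either group, and nothing in the control rule balances it. The wording on the controls' treatment does not help, because the abbreviation used there stands for a toxicity and not for a treatment regimen.

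If chemotherapy is more common among women with toxicity, the unadjusted group contrast mixes two differences: toxicity against no toxicity, and chemotherapy against none. A lower level of SCFA producers in the toxicity group could then be read as a feature of toxicity when some or all of it reflects treatment history. This would remain even if all women had been irradiated alike. The abstract presents the findings as groundwork for a randomized trial, so a misread group contrast could carry forward.

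**Working it through.** **1. What the plan fixes.** There are 19 women per group, tests are two-sided at 0.05, and the group test is an unadjusted Mann–Whitney. The total of 38 is stated without an effect size, SD or power, so there is no derivation to reproduce. For scale, the difference detectable with 80% power by the normal approximation is (1.960 + 0.842) × √(2/19) = 0.91 SD.

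**2. What the plan does not give.** It gives no chemotherapy share in either group, no chemotherapy–toxicity odds ratio, and no chemotherapy effect on the microbiota at sampling. Everything below rests on assumptions.

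**3. Bias.** Let p1 and p0 be the chemotherapy shares in the toxicity and control groups, and d the chemotherapy effect in SD. With no other relation between toxicity and microbiota, bias = d × (p1 − p0).

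Assume that half of all 38 women had chemotherapy, so p0 = 1 − p1. The odds ratio is then (p1/p0)², and p1 = √OR / (1 + √OR):
- OR 2: p1 = 1.414/2.414 = 0.59, p0 = 0.41
- OR 4: p1 = 2/3 = 0.67, p0 = 0.33
- OR 8: p1 = 2.828/3.828 = 0.74, p0 = 0.26

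**4. False-positive rate.** Simulated Mann–Whitney test, 19 vs 19, 4,000 runs per cell, no true toxicity–microbiota difference, no allowance for tumor-site matching. Each cell shows bias, then rejection rate:

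| Odds ratio | d = 0.5 SD | d = 1.0 SD | d = 1.5 SD |
|---|---|---|---|
| 2 | 0.09 SD, 4.9% | 0.17 SD, 7.6% | 0.26 SD, 8.4% |
| 4 | 0.17 SD, 6.7% | 0.33 SD, 13.5% | 0.50 SD, 22.0% |
| 8 | 0.24 SD, 10.8% | 0.48 SD, 25.5% | 0.72 SD, 44.0% |

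A repeat with 6,000 runs per cell gave 5% to 43%.

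**5. Check with other assumed shares** (20,000 runs each). At d = 1.0 SD, shares of 70/50%, 80/40% and 90/30% give biases of 0.20, 0.40 and 0.60 SD and rejection rates of 7.6%, 18.8% and 37.3%. At d = 0.5 SD the rates are 5.4%, 8.4% and 13.1%.

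**6. Does the remedy work?** With equal shares (60/60%), the plain test rejects in 4.7% to 4.8% of runs for d from 0.5 to 1.0 SD. With unequal shares, a rank test stratified by chemotherapy (van Elteren) held the rate at 4.4% to 5.0% in every cell of the table.

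**7. Pre/post comparison.** Chemotherapy completed before ozone is the same for both samples of a given woman, so the Wilcoxon signed-rank comparison cannot pick it up.

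**The case against.** **A chain is not a confounder.** The concluding statement of Section 2 describes chemotherapy changing the microbiota and the microbiota driving toxicity. In that chain alone, a group difference in taxa is real. The simulation would not apply either: without a microbiota–toxicity link, the odds ratio would be 1 and the false-positive rate 5%. This stands against reading that statement by itself as proof of a common cause. Confounding needs a second route from chemotherapy to toxicity. The direct epithelial injury in part (a) makes one plausible but does not prove it.

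**Persistence.** Women have completed treatment, and toxicity has lasted at least three months. The only statement that dysbiosis persists concerns radiotherapy, and no passage says that these women received 5-FU or irinotecan. This stands, and it is why the low end of the range, with no inflation, cannot be excluded.

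**The ozone question is untouched.** This also stands. A reader might infer that the bias favors the ozone hypothesis. It does not: a distorted group difference at baseline cannot produce a change within the same woman.

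**Matching, caveats and the analysis plan.** Tumor-site matching may balance chemotherapy in part, but eligibility lets it vary within a site. The list of confounders to record is open, but recording does not adjust a test. The caveat on causal conclusions cites design and sample size only. A stratified test or an exposure table may well sit in an analysis plan not shown, and their absence here is no fault. The matching rule, however, is a recruitment decision stated in this article, and with 19 per group poor overlap cannot be fully repaired afterwards.

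**Conclusion.** The point holds for the toxicity-versus-control contrast: as stated, the control rule allows prior chemotherapy to confound it. It does not extend to the within-patient ozone analysis.

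The size is unknown. In the middle of the assumed range (odds ratio 4, effect 1 SD), the bias is 0.33 SD, about a third of the 0.91 SD that 19 per group can detect, and the false-positive rate is about 13% instead of 5%. The table's extremes run from no inflation to about 44%. These figures assume that half of all women had chemotherapy, that its link to toxicity bypasses the microbiota, that its effect lasts to sampling, and that tumor-site matching removes none of the imbalance. Partial balance by tumor site would lower them.

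A reader might infer that the article establishes chemotherapy as a common cause, or that a false result in this contrast is likely. The documents support neither: they make the confounding route plausible and leave it uncontrolled. The change should be made before controls are selected, but the point does not invalidate the study.

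**What to change.** In the control definition in Section 5 and in Table 1, add prior chemotherapy (none vs any) as a matching factor where a match is available. Where it is not, make the group comparison with a rank test stratified by chemotherapy (none vs any) in place of the plain Mann–Whitney. In either case, show chemotherapy exposure by group beside the microbiota contrast. That display helps even if shares are equal on average: for shares of 30% to 70%, a gap of four or more women out of 19 arises by chance in about 21% to 26% of samples.

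Chemotherapy history should be available from the chart, and controls are still to be chosen, so the change is small. The price is a somewhat narrower control pool and some loss of precision if strata are thin. None vs any does not deal with differences between agents, although the article itself says that "the specific changes can vary based on the chemotherapeutic agent"; name that as a limitation of the group contrast. The pre/post analysis needs no change.
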